**Figure 1 figure1:**
[figure not shown]
Flow diagram of the user interface.

**Figure 2 figure2:**
[figure not shown]
Screenshots of the various layouts of the app: vaccination schedule layout (top left), resources layout (top right), notification detail layout (bottom left), and about us layout (bottom right).

### Development of the AI-Enabled App

AI is being applied in this study in two different manners. First, AI is being applied to the baseline data and RCT results from a previous study, which is based on an automated SMS text message and voice call intervention [25]. Paigham-e-Sehat is a recently completed study that includes data from 3300 children, in which RCI-related messages were sent to caregivers via SMS text messages or automated calls to improve their children’s vaccine coverage at 6, 10, and 14 weeks of age. An AI model, using decision tree classification, random forest, naïve Bayes, and k-nearest neighbor algorithms, generated through that study is being used to train the system for predicting the likelihood of a family defaulting from subsequent RCI visits. This system will be tested during this study by validating the system’s prediction ability against the actual outcome of this study. Further, the important predictors and barriers identified in the previous study will be used for extending the work on data obtained from this study [25]**.** After the availability of the study results, factors related to the effect of users’ app behavior on the vaccination outcomes, including their preferred modes, timing, and interactivity with the app, will be analyzed through pattern recognition using a mixture of hidden Markov models. These findings will then be used to train the next version of the app to automatically adjust to individual user behaviors that have been found to be effective in improving RCI coverage (eg, the pattern recognition may identify a cluster of participants that have a better chance of getting their children immunized if they interact with app notifications during the weekend, when they are more likely to plan the next week).

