### Development of the Smartphone App

This smartphone app, as part of the Capacity Building in Technology-Driven Innovation in Healthcare (CoNTINuE) project, will be developed on an Android platform, as 95% of smartphone users in Pakistan use Android phones [26]. Functionality validation exercises will be carried out using cognitive validation and cultural probes before using the app in this research. The app will be installed on the phones of the participants in the intervention arm by the study administrators. Once the app has launched and privacy policies have been accepted, the participants will be asked to enter information into the app, including their child’s medical record number, their child’s date of birth, their preferred mode of messages such as audio or text, their language and time preferences to receive the messages, and the barriers they face to vaccinate their child; these features will help personalize the type and content of messages they will receive. The data will be stored in local secured systems and immediately anonymized using digitally available tools to ensure privacy and avoid any potential identity breach.

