After entering the enrollment data, the phone will need to be connected to the internet for a few minutes to allow for necessary content to be downloaded, which will enable timely notifications in the future. At the enrollment site, free Wi-Fi will be available for the participants. However, in the event of a disruption in downloading the app or prolonged time consumption due to the size of the app, an alternate Wi-Fi connection, whose cost is covered by the project, will be provided to download the app. This feature of one-time downloading of the data allows for the app to be functional even in the case of internet unavailability. Once the content is downloaded, the first screen to be displayed will be the app logo layout followed by the main home layout. The user can then navigate to the (1) *vaccination schedule* layout, (2) *resources* layout, (3) *notification detail* layout, or (4) *about us* layout pages, as shown in Figures 1 and 2. This app will be developed to catalyze a behavioral change in its users through its many functionalities. In the *vaccination schedule* layout, a calendar indicating the child’s specific, scheduled vaccination days will be displayed. In the *resources* layout, the users will be able to access the official websites of the EPI, the AKUH CHC, and World Health Organization vaccines, among others. The *notification detail* layout will display notifications every week regarding upcoming vaccinations or educational messages. The notifications will be displayed as summaries, and additional information and content from the text or audio message will be able to be accessed upon clicking the individual notification. The notifications will be delivered in the participant’s preferred language (ie, Urdu, English, Sindhi, Roman Urdu, and Roman Sindhi), preferred mode of messaging (ie, text or audio), and preferred time for receiving the notifications (ie, morning, afternoon, or evening). Lastly, the *about us* layout will provide insight into the vision of the CoNTINuE project. These navigation panels and their labels will also be displayed in the preferred local language. Also, at the time of enrollment, a detailed walk-through process of the app will be conducted with the caregivers.

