## Results

Pretrial, qualitative, in-depth interviews were conducted in February 2020. The main theme extracted was that mothers are the decision makers of the family regarding child health. The majority of the caregivers said that they preferred text messages rather than audio messages because (1) they can be stored in mobile phones and can be accessed anytime, (2) sometimes audio is not clear, and (3) audio cannot be played everywhere, but text can be read easily. There were no time preferences regarding the receipt of app notifications by the caregivers. Most of the parents and caregivers used Android-based smartphones. English and Urdu were the preferred languages for immunization-related messages. According to the caregivers, the mobile app should have information regarding the doses and purpose of all the childhood immunizations to be given until 5 years of age. In addition to immunization-related messages, the parents were also interested in monitoring their children’s health progress through the app. Parents found the idea of a mobile app helpful, as it will remind them of their children’s vaccine due dates, will provide additional information regarding immunization, and will have no installation charges.

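### App behaviours that users choose within one arm are to be treated as effective, but the analysis can show only who vaccinates, not what works

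*Protocol article*

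**What the plan says.** Under Development of the AI-Enabled App, the protocol article sets out a step to follow the trial results. It will examine "factors related to the effect of users’ app behavior on the vaccination outcomes, including their preferred modes, timing, and interactivity with the app", and these "will be analyzed through pattern recognition using a mixture of hidden Markov models". The next version of the app is then to "automatically adjust to individual user behaviors that have been found to be effective in improving RCI coverage". The worked example is a cluster of families with "a better chance of getting their children immunized if they interact with app notifications during the weekend".

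Three other places fix what this analysis can rest on:

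- Development of the Smartphone App: "The app will be installed on the phones of the participants in the intervention arm by the study administrators". There is no app behaviour to observe in the control arm.
- Same section: on first use caregivers enter their preferred mode, "their language and time preferences to receive the messages, and the barriers they face to vaccinate their child". Mode and time slot are therefore the caregiver's choice.
- Trial RCT and Randomization: the only random allocation is 1:1 between app and standard care. No feature inside the app is allocated at random.

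Study Objectives makes it the second primary objective to evaluate whether an AI model can be built into the app to improve coverage and change behaviour.

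**The concern.** The passage speaks of effects and of effective behaviours, and commits to acting on them, but describes a comparison that randomisation does not protect. Two routes can produce an association without any effect.

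1. **Common cause.** A motivated caregiver both opens notifications and brings the child. Interaction then marks motivation.
2. **Reverse order.** Messages run weekly until 14 weeks of age, so the interaction log spans the 10-week dose. What a caregiver does in the app after that dose was given or missed may be a consequence of the outcome.

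A mixture of hidden Markov models groups families by behaviour pattern. Grouping alone removes neither problem. At stake is what may be concluded for the AI objective: an app tuned to habits that merely mark motivated families need not raise coverage in anyone.

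**Working it through.** The plan gives no figure for this step, so there is none to reproduce. The check asks how large a difference can arise when the behaviour has no effect.

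**Inputs from the article.** App arm of 164 infants, an assumed app-arm coverage of 60%, and 10% dropout (Sample Population and Size); a 10% increase as the target (Primary Outcomes).

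**Assumed inputs, not in the article.** Half the app families are motivated. Coverage is v₁ in motivated and v₀ in other families, averaging 60%. Weekend interaction has probability b₁ and b₀ in the two groups. Within each group, interaction does not alter vaccination.

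**Formulas** (the equal halves cancel):

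- Coverage in weekend users = (b₁v₁ + b₀v₀) / (b₁ + b₀)
- Coverage in the rest = [(1−b₁)v₁ + (1−b₀)v₀] / [(1−b₁) + (1−b₀)]

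**Middle setting**, v = 75%/45%, b = 60%/30%:

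- Weekend users: (0.60×0.75 + 0.30×0.45) / 0.90 = 0.585/0.90 = 65.0%
- The rest: (0.40×0.75 + 0.70×0.45) / 1.10 = 0.615/1.10 = 55.9%
- Difference: 9.1 points

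| v₁/v₀ | b₁/b₀ | Weekend users | The rest | Difference with no effect |
|---|---|---|---|---|
| 70%/50% | 60%/40% | 62% | 58% | 4 points |
| 75%/45% | 60%/30% | 65.0% | 55.9% | 9 points |
| 80%/40% | 70%/30% | 68% | 52% | 16 points |

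If the 164 app families were simply split by this behaviour and compared at the two-sided 5% level, the chance of a nominally significant result would be about 8% in the first setting and 55% in the third. The hidden Markov analysis is not a two-group test, so these figures show only the order of size.

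**Would randomising notification timing inside this trial answer the question?** Take two timing groups, 164/2 = 82 each, and a 10-point difference around 60% (55% versus 65%):

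- Standard error under no difference: √(2×0.60×0.40/82) = 0.0765; under the alternative: √[(0.55×0.45 + 0.65×0.35)/82] = 0.0761
- Power = Φ[(0.10 − 1.96×0.0765)/0.0761] = Φ(−0.66) ≈ 26%
- After 10% dropout (74 per group): about 24%
- Smallest difference with 80% power: about 21 points (22 after dropout)
- Group size needed for 10 points with 80% power: about 376

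Eighty-two is a ceiling, since families enrolled before such a change would not count.

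**The case against.** The strongest reply is that no trial conclusion depends on this step. It comes after the results and serves a later product, and no listed primary or secondary outcome uses it. The only AI outcome with a target is 85% accuracy in predicting default, and prediction needs no causal argument. The Abstract words the AI objective more modestly, as whether a model can be incorporated. The weekend example is itself hedged: the pattern recognition may identify such a cluster. All of this stands, and it limits the weight of the point. It does not remove it, because the sentence on the next version goes beyond prediction and commits to acting on behaviours as effective.

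It is also fair that the sizes rest on assumed inputs, with the mildest setting giving only 4 points. And the article's silence on the logging window is no fault in itself, since a condensed article may leave that to a fuller document. The due-date restriction belongs to the remedy; its absence is not charged as an omission.

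A reader might infer that notification timing should be randomised in the current trial at almost no cost, since day of week is not a listed preference and the interviews found that "There were no time preferences regarding the receipt of app notifications by the caregivers". The documents do not carry that far:

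- Those interviews were with 15-20 purposively sampled parents.
- Time choice is one of the features that personalise the intervention under test.
- The Abstract reports enrolment in process, so an experimental factor would enter a running trial with an ethics-approved protocol.
- Assigning delivery time would not randomise interaction, which is the article's own example.
- The precision is poor, as shown above.

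A reader might also infer that the trial's main result is compromised. It is not: that comparison is randomised and analysed by intention to treat.

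**Conclusion.** The point holds within limits. As written, the step would present self-chosen behaviours in a single arm as effective, although they can mark motivation or follow from the outcome. It can identify who vaccinates, not what works. With no true effect, spurious differences of about 4 to 16 points arise, assuming that half the families are motivated and using the coverage and interaction rates tabulated above. None of those rates comes from the article, so the range shows what is possible and does not forecast the bias. The consequence is confined to an exploratory, post-trial step and to what may be claimed for the AI objective.

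**What to change.** In Development of the AI-Enabled App:

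1. Use only app behaviour logged before each dose's due date when relating it to that dose.
2. Describe the findings on mode, timing and interactivity as predictors of default or as hypotheses, and drop the language of effect and effectiveness.
3. State that no behaviour or timing will be called effective until it has been tested by random assignment, for example of notification day in a later app version.

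This is a change of wording and an analysis rule. It costs a weaker claim from the exploratory step and the interaction data after each due date. Randomising notification timing in the current trial is optional and is not part of this fix; if done, its low precision should be stated beforehand.

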### Trial RCT

#### Study Design, Settings, and Timeline

The study design is an RCT, consisting of two parallel arms with the allocation of 1:1 to the intervention group or the standard care group (ie, control group). After obtaining informed consent, eligible infants and their caregivers will be randomly allocated into one of two groups using randomly generated computer assignments, where allocations will be placed in sealed opaque envelopes to be opened at the time of enrollment. IDs will be generated in blocks, with 6 cases in each block. Details of each group are as follows:

Intervention group: the intervention group, in addition to the standard counseling group, will receive text, voice, pictorial, and video messages regarding vaccinations; messages will be received once a week until the child turns 14 weeks of age.Control group: the control group will receive one-time, standard, verbal counseling at the time of the initial visit for on-time EPI vaccines at 10 and 14 weeks of age, as recommended by the EPI and the government of Pakistan.

The trial was registered at ClinicalTrials.gov (NCT04449107).

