### Study Site

This study will be conducted at the AKUH in Karachi, Pakistan. The caregivers visiting the vaccination center at the AKUH Community Health Center (CHC) will be enrolled in the study.

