#### Sampling Methodology

The study staff will approach families visiting the AKUH CHC vaccination center, who have brought an infant for their 6-week RCI. Staff will explain the study objectives to the parents or caregivers. If the parent or caregiver is interested in the study, the infant will be evaluated for enrollment. One child per household will be selected. In a household where there is more than one child due for a 10- or 14-week vaccination, a random selection will be made by a program designed in the mobile phone device. After meeting the eligibility criteria, informed consent will be obtained, and the infant will be enrolled in the study.

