#### Randomization

The intervention and control group ratio will be 1:1; the randomization list will be generated through computer assignments with blocks of 6 children; participant allocation will be placed in sealed opaque envelopes that will be opened at the time of enrollment after informed consent.

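### A single published block size of 6 at one centre weakens the envelope concealment: up to a quarter of allocations can be known in advance if recruiters track the sequence

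*Protocol article*

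**What the plan says.** The block size is stated twice in the protocol article, under Study Design, Settings, and Timeline ("IDs will be generated in blocks, with 6 cases in each block") and under Randomization ("the randomization list will be generated through computer assignments with blocks of 6 children"). No other size is mentioned. Randomization also gives the ratio ("The intervention and control group ratio will be 1:1") and the concealment method: "participant allocation will be placed in sealed opaque envelopes that will be opened at the time of enrollment after informed consent".

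Four other places bear on how far the sequence can be followed:

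- **Study Site** names one recruiting centre: "The caregivers visiting the vaccination center at the AKUH Community Health Center (CHC) will be enrolled in the study". No stratification factor is given anywhere, so the article describes one list.
- **Development of the Smartphone App** makes the arm visible once assigned: "The app will be installed on the phones of the participants in the intervention arm by the study administrators".
- **Sampling Methodology** puts recruitment before allocation: "The study staff will approach families visiting the AKUH CHC vaccination center, who have brought an infant for their 6-week RCI". Eligibility is then evaluated, and consent follows.
- **Inclusion and Exclusion Criteria** require a basic level of skill with an Android phone, and exclude families who do not intend to come back to the hospital for the 10- and 14-week visits.

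The Results paragraph of the Abstract reports that trial enrolment was under way at publication.

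**The concern.** An opaque envelope hides the next card, but not what the earlier cards imply. With a constant block of 6 at 1:1, each block holds three allocations to each arm. Once three of one arm have appeared, the rest of the block is known. Opening the envelope only after consent does not prevent this, because the deduction can be made before a family is approached or its eligibility is settled.

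What is at stake is selection bias. Smartphone skill is judged by staff. The intention to return is the family's own, but staff must establish it, and it lies close to the primary outcome of attending for vaccination. If knowledge of the next arm influenced who was approached or accepted, the arms could differ in motivation before any app was installed. An intention-to-treat analysis would not remove that difference.

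**Working it through.** The article gives no figure for predictability, so there is none to reproduce.

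**Inputs.** Block size 6 and ratio 1:1, so 3 + 3 per block (Study Design, Settings, and Timeline; Randomization). Total 328 infants, 164 per arm (Sample Population and Size). One list (Study Site; no stratification stated). *Assumption, not in the article:* the observer knows the block size and where each block starts, and has followed every earlier assignment in order.

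**Step 1. Certain allocations per block.** There are C(6,3) = 20 equally likely sequences. An allocation is certain once one arm's three places are used.

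| Place in block | Certain when | Chance |
|---|---|---|
| 1 to 3 | never | 0 |
| 4 | first three all in one arm | 2/20 = 10% |
| 5 | first four split 3:1 | (4 + 4)/20 = 40% |
| 6 | always | 100% |

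Expected number: 0.10 + 0.40 + 1.00 = 1.5 of 6, or 25%. The closed form agrees: B/(B/2 + 1) = 6/4 = 1.5. Of all blocks, 60% have one certain allocation, 30% have two and 10% have three.

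**Step 2. Over the trial.** 0.25 × 328 = 82. Counted by blocks, 328 = 54 × 6 + 4, so 54 × 1.5 = 81, plus 0.1 from the last four places. The range is about 81 to 82.

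**Step 3. Best guess.** Always guessing the arm with more places left gives an expected number correct per block of B/2 + (2^B / C(B, B/2) − 1)/2 = 3 + (64/20 − 1)/2 = 4.1. That is 4.1/6 = 68.3%, against 50% with no information.

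**Step 4. Alternatives.** Larger fixed blocks help only a little. The certain share is 1/(B/2 + 1), which is 20% for size 8, 16.7% for size 10 and 14.3% for size 12. Randomly varied sizes were simulated with 300 lists of 328 and an observer who knows the set of sizes but not their order:

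| Scheme | Known with certainty | Best guess correct |
|---|---|---|
| Fixed 6 | 24.6% (exact 25%) | 68.3% |
| Varied 4, 6 | 5.4% | 69.3% |
| Varied 4, 6, 8 | 2.3% | 68.0% |

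**Step 5. Possible size of bias (illustration).** By symmetry the 82 certain places split on average 41 to each arm, and 41/164 = 25%. Suppose every one were steered, and the families steered to the two arms differed by d percentage points in underlying coverage. The bias would be 0.25 × d. The article gives no d. For assumed values of 10, 20 and 30 points the bias is 2.5, 5 and 7.5 points. The sample size assumes an increase of 60 − 40 = 20 points, and the primary outcomes name a 10% increase. This is a worst case, not an estimate.

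**The case against.** The strongest reply is that the 25% is a ceiling resting on conditions the article does not establish.

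- The article does not say who opens the envelopes; both descriptions are in the passive.
- Families are approached by study staff and the app is installed by study administrators. Whether these are the same people, or share a log, is not stated. If assignments are not pooled, the predictable share falls.
- The article describes staff approaching families who come for the 6-week visit. It does not describe picking among them.
- Open-label and unstratified are inferences; neither term is used.
- Who holds the list, and what recruiters are told, are matters that an article may leave to the full protocol.

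All of this stands and limits the claim. A reader might infer that recruiters can in fact foresee a quarter of allocations, or that concealment is defeated. The documents support neither. Even for a fully informed observer three quarters of allocations are not certain, the first three places in a block never are, and nothing suggests that staff would steer families.

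A further fair objection is that the 68% best-guess rate should not be charged to the fixed block, because varied blocks leave it almost unchanged. That is correct, so the case for change rests on the certain allocations alone.

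The reply does not remove the point. The single block size is a stated choice, not an omitted detail. It was published during recruitment, and one arm receives a visible installation.

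**Conclusion.** The concern holds in a limited form. The fixed block of 6 weakens concealment: up to 25% of allocations, about 82 of 328, can be known in advance by someone who knows the block size and follows the whole sequence. The arithmetic is exact; the conditions behind it are assumptions, and the true share is lower to the extent that they fail. The effect on the trial is a risk of selection bias of unknown size, not a demonstrated distortion. Such bias could not be reliably repaired in the analysis, and the exposure is cheap to reduce, so the change is worth making.

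**What to change.** For remaining enrolment, generate the list with randomly varied block sizes, for example 4, 6 and 8, and do not disclose the sizes or their order to recruiting staff. The envelopes and the order of eligibility, consent and opening can stay as they are. On the simulation above, certain allocations fall from 25% to about 2% even for an observer who knows the set of sizes; the best-guess rate stays near 68%.

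The cost is a new list and a new set of envelopes. The statistical downside is a slightly larger possible imbalance at the end. With a largest block of 8, the arms could differ by up to 4 when enrolment stops. Blocks of 6 run to exactly 328 could end with a difference of at most 2, because the last four places split 2:2 or 3:1. Either is negligible at about 164 per arm. The sample size, outcomes and analysis do not change. Infants already randomised are unaffected; the article does not say how many there were, so the share of the trial that would benefit is unknown.
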